## Introduction

### Background

Aging is associated with the onset of postlingual sensorineural hearing loss (SNHL), which refers to hearing loss (or deafness) arising from the pathology of either the inner ear organs or the vestibulocochlear nerve after language acquisition. SNHL accounts for approximately 90% of hearing loss cases in adults and is insidious, progressing from normal (pure tone average [PTA]=0-25 dB) to mild (PTA=26-40 dB), to moderate (PTA=41-70dB), to severe (PTA=71-90 dB), and ending with profound (PTA >91 dB) or total hearing loss. However, more alarming are the sequelae of SNHL that might include rapid cognitive decline [1], impaired psychosocial functioning [2], increased risk of falling [3], and increased risk of incident dementia [4,5]. Recent work, including a meta-analysis of 33 studies [6], reported that SNHL is independently related to both cognitive impairment [7] and the risk of incident dementia [4] and perhaps, most critically, the degree of hearing loss predicts both the degree of cognitive impairment [1] and risk of dementia [4]. Furthermore, recent work suggests that 9% of dementia risk over the life course could be eliminated by avoiding the effects of hearing loss [5].

The scale of these problems is brought into sharp focus in the light of SNHL being the most prevalent chronic condition affecting older adults in developed countries (16%-20%) [8-10] and the second leading cause of years lost to disability globally [11]. Sadly, SNHL often goes undiagnosed and untreated or undertreated [12,13], and the sequelae of SNHL, incident dementia in particular, impose a significant burden not only on individuals and their families and friends but also on national health budgets [14,15]. A recent nationwide study in Australia found that all forms of hearing loss affected 14.5% of Australians (3.6 million people), especially those aged >50 years, with direct costs to the Australian economy of almost Aus $15.9 billion [16]. Furthermore, the number of Australians affected is expected to grow to 18.9% of the population by 2060, thereby slowing or stopping the progression of SNHL is a public health imperative.

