**Figure 1 figure1:**
[figure not shown]
Hypothesized relationships associated with first-time hearing aid usage.

This functional alteration is thought to stem from the loosening of associations between memory and phonological processes and viseme (visual aspects of phoneme pronunciation) processes as SNHL progresses [29] (ie, altered functional connectivity), leading to these plastic brain changes. The phonological processing specialization of the left posterior temporal lobe appears to be preserved, whereas right lateral homologues that are predominantly involved in processing environmental sounds are repurposed to accommodate enhanced visual processing that aids the reading of visual cues (eg, lip-reading) and phonological processing capabilities [21,28,30]. Furthermore, the right anterior part of the superior temporal gyrus that normally performs voice and speaker identification functions is also repurposed for reading visual cues; however, this plastic alteration can be reversed by auditory rehabilitation [31].

Fortunately, a recent investigation suggests that hearing aids worn by individuals with SNHL can preserve or improve auditory and cognitive functioning [32-34] in addition to improving psychosocial well-being [33,35-38]. This suggests that stimulation, as afforded by hearing aid use, can preserve auditory functions and aural specificity and that hearing aids have a protective effect against the deleterious plastic alteration of auditory areas [39].

Alarmingly, however, approximately 90% of people with mild hearing loss, approximately 60% with moderate to severe hearing loss, and approximately 70% aged 65-84 years do not use hearing aids [40]. Furthermore, it often takes about 10 years for an individual to recognize that they have a hearing problem and then act, including obtaining hearing aids, to address this problem [41]. Critically, almost two-thirds of older adults with a hearing impairment do not use hearing aids [42].

This prospective cohort study, in which magnetic resonance imaging (MRI) is utilized in combination with clinical, neuropsychological, and hearing tests, aims to investigate the neurocognitive and psychosocial effects of wearing hearing aids in older adults with SNHL (ACTRN12617001616369).

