## Methods

### Study Design

The study is a prospective cohort design evaluating the effect of the hearing aid use on cognition, psychosocial factors (eg, depression and social interaction), and neural function. We will recruit 2 participant groups of similar size consisting of people with mild to moderate SNHL. Of note, group randomization is not possible in this study; however, the groups will be matched as much as possible in terms of the degree of hearing loss.

Group A: Patients with SNHL who have used hearing aids for, at least, the previous 12 months and plan to continue using their hearing aids for the next 6 months.Group B: Patients with SNHL who have never used hearing aids before and who will be willing to wear hearing aids for the next 6 months.

All participants would be asked to complete, at 2 time points (t) including baseline (t=0) and follow-up (t=6 months), tests of hearing and psychosocial and cognitive function and attend an MRI session.

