### Study Power Analysis

With 30 consented participants in each group with a significance level of 5%, the power of 80%, and controlling for age, gender, and level of education, the baseline analysis of covariance (ANCOVA) model for spatial working memory performance can detect effect sizes of *d*=0.63 for between-group differences. Allowing 10% attrition in the 6-month follow-up period, a sample size of 27 in each group with a significance level of 5% and power of 80%, a significant group-by-time interaction effect can be detected for a large effect size of *d*=0.77. This study is based on the assumption that an effect size of *d*

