#### Cognitive Data

The SUCCAB performance measure for spatial working memory will be used as the primary SUCCAB measure; this measure has been found to be particularly effective in measuring short-term changes in cognition of the elderly [52] and is calculated by dividing the response accuracy by the reaction time for a spatial working memory task. Using this and other SUCCAB performance measures, baseline values for the 2 groups will be compared using an ANCOVA analysis, controlling for age, gender, and education level. In addition, changes in these values over time will be compared for the 2 groups of respondents using an ITT RMMM, controlling for age, gender, and education level and any variable that differs markedly between the groups at the baseline.

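### The baseline SUCCAB ANCOVA leaves out degree of hearing loss, so any hearing difference left after approximate matching biases the cross-sectional user versus never-user comparison

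*Protocol article*

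**What the plan says.** - **Baseline model** (Primary Statistical Analyses, Cognitive Data): "baseline values for the 2 groups will be compared using an ANCOVA analysis, controlling for age, gender, and education level". It applies to the primary SUCCAB measure, spatial working memory, and to the other SUCCAB measures.
- **Power** (Study Power Analysis): the same model with the same three covariates, "controlling for age, gender, and level of education, the baseline analysis of covariance (ANCOVA) model for spatial working memory performance", has its own detectable effect of d=0.63 with 30 per group.
- **Longitudinal model** (Cognitive Data, next sentence): the repeated measures mixed model uses these three covariates and also "any variable that differs markedly between the groups at the baseline". That extension is not attached to the baseline ANCOVA.
- **Design** (Study Design): "group randomization is not possible in this study", and "the groups will be matched as much as possible in terms of the degree of hearing loss". No tolerance is given.
- **Prognosis** (Background): "the degree of hearing loss predicts both the degree of cognitive impairment [1] and risk of dementia [4".
- **Severity admitted**: mild or moderate loss (Eligibility Criteria), which Background defines as "to mild (PTA=26-40 dB), to moderate (PTA=41-70dB".
- **Non-use of aids by severity** (Background, after Figure 1): "approximately 90% of people with mild hearing loss, approximately 60% with moderate to severe hearing loss".
- **Availability**: hearing is assessed at the clinics before the first scan is scheduled (Recruitment and Screening), with thresholds taken in both ears (Pure Tone Audiometry in Each Ear).

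**The concern.** On the article's own statements, hearing severity is related both to group (aid use is commoner in worse hearing) and to the outcome (worse hearing goes with worse cognition). In a non-randomized comparison that is a confounder. Best-effort matching reduces it, but the baseline model has nothing to catch what remains.

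If long-term users have the poorer hearing, a real cognitive advantage of users is masked, or a false deficit appears. If never-users have the poorer hearing, the reverse happens. This ANCOVA stands under the primary analyses and has its own power figure, so its result is likely to be read as more than a descriptive table. The covariate list is a stated model choice, not a detail left to a fuller document.

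**Working it through.** **1. The plan's own figure.** Take 30 per group, 5% level, 80% power; the article does not state sidedness. Two-sided, with three covariates that explain no variance (noncentral t, 60 − 2 − 3 = 55 df), the detectable d is 0.736. To reach 0.63 the covariates must explain 1 − (0.63/0.7363)² = 0.27 of the variance. One-sided by normal approximation it is 0.642. So 0.63 is reachable only under an unstated variant. That is a separate matter and does not alter this point.

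**2. Which way would hearing differ before matching?** The quoted non-use rates imply use of about 10% in mild and 40% in moderate to severe loss. Assume a source population that is half mild:
- mild among users: 0.5×0.10 / (0.5×0.10 + 0.5×0.40) = 0.05/0.25 = 20%
- mild among non-users: 0.5×0.90 / (0.5×0.90 + 0.5×0.60) = 0.45/0.75 = 60%

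With 30% mild the pair is 10% and 39%; with 70% mild it is 37% and 78%. Users would have the poorer hearing in each case. The 60% figure also covers severe loss, which this study excludes, and all of this is before matching.

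**3. Bias.** Let ρ be the partial correlation of PTA with the outcome given age, gender and education, and δ the standardized PTA difference left after matching. Neither is in the document; both are assumed. The unadjusted group difference is then biased by ρ×δ in SD units. For scale, if PTA were uniform over 26–70 dB, its SD would be 44/√12 = 12.7 dB, so 0.25 SD is about 3 dB and 0.5 SD about 6 dB.

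**4. Type I error given that imbalance.** Noncentral t, 55 df, two-sided 5%, noncentrality = bias × √(30/2) = 3.87 × bias:

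| ρ | δ | Bias (SD) | Share of 0.63 | Type I error |
|---|---|---|---|---|
| 0.2 | 0.25 | 0.05 | 8% | 5.4% |
| 0.3 | 0.25 | 0.075 | 12% | 5.9% |
| 0.4 | 0.25 | 0.10 | 16% | 6.7% |
| 0.2 | 0.5 | 0.10 | 16% | 6.7% |
| 0.3 | 0.5 | 0.15 | 24% | 8.8% |
| 0.4 | 0.5 | 0.20 | 32% | 11.9% |

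**5. Precision with PTA added.** The standard error is multiplied by √((1 − ρ²)(1 + δ²/4)):
- ρ=0.4, δ=0.25: √(0.84 × 1.0156) = 0.92, detectable d 0.63 → 0.58
- ρ=0.3, δ=0.5: √(0.91 × 1.0625) = 0.98, detectable d → 0.62
- ρ=0.2, δ=0.75: √(0.96 × 1.1406) = 1.05, detectable d → 0.66

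**The case against.** **The study's hypotheses lie elsewhere.** This stands. Every hypothesis under Study Hypotheses concerns change after six months, and baseline relationships are only to be explored. A reader might infer that the main analysis also ignores hearing loss. The text does not support that: the clause in the mixed model can bring PTA in.

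**Severity is already controlled by design.** This stands in part. Matching and the restriction to mild or moderate loss both limit the imbalance. But matching is best-effort without a stated tolerance, and the admitted range is 44 dB wide.

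**Imbalance is not shown to be likely.** A reader might infer from the recruitment routes that the groups will differ in hearing. Recruitment and Screening does not say so: clinics supply both groups, and nothing there gives PTA by group. Only the usage rates point to a difference, and only before matching.

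**Large figures are easy to produce.** With ρ=0.4 and δ=0.75 the bias is 0.30 SD and the type I error 21%. But 0.75 SD is about 9.5 dB, which would mean that matching had largely failed. Excluding low MMSE scores and restricting the PTA range would also tend to weaken the correlation. These values should not be presented as expected.

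**PTA may partly be a result of aid use.** Background says aids may preserve auditory function, so adjustment could remove part of the difference being estimated in long-term users. This stands as a reason to report both models. It does not justify showing only the one without PTA.

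**Conclusion.** The point holds for the baseline SUCCAB ANCOVA and its power statement, and for nothing wider. The model omits a variable that the article names as prognostic and that was only approximately matched, so any residual PTA difference biases the cross-sectional comparison.

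The amount cannot be known from the document. With ρ between 0.2 and 0.4, it is 0.05 to 0.10 SD (type I error 5.4% to 6.7%) if matching is within 0.25 SD, and 0.15 SD (8.8%) in the middle case of ρ=0.3 and δ=0.5. These figures assume a linear effect, two-sided testing and 30 per group.

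A reader might also infer that adding PTA returns the error rate to 5%. That would be so only if PTA were the sole confounder and acted linearly, which cannot be claimed for self-selected groups. Nor is precision the main argument: over ρ of 0.2 to 0.4 and δ of 0.25 to 0.75 the standard error changes by a factor of 0.92 to 1.05. The case for the change is that it removes one foreseeable source of bias at little cost.

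**What to change.** - In Cognitive Data, prespecify continuous baseline PTA (better-ear or two-ear mean, chosen in advance) as a covariate in the baseline SUCCAB ANCOVA beside age, gender and education, whether or not the groups turn out to differ on it.
- Align the covariate list in Study Power Analysis.
- Report the model without PTA alongside. State that PTA in long-term users may partly reflect past aid use, and that adjustment does not remove other confounding.

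**Cost:** two sentences of text and one degree of freedom (55 to 54). No new data are needed, since audiometry is already done in everyone. The standard error could be about 5% larger if PTA is imbalanced but only weakly prognostic (ρ=0.2, δ=0.75), and would be somewhat smaller if matching works and PTA is prognostic.

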### Primary Statistical Analyses

In this study, repeated measures mixed model group (no hearing aid vs hearing aid users) x Time (Time 1 vs Time 2) analysis (RMMM) will be used for all analyses. The missing data will be accommodated in this analysis; however, in the case of whole-brain fMRI analyses, only completed protocol participants will be included. In the ITT RMMM analyses, the autoregressive (AR) dependence will be assumed.

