**Mood and Social Interaction Data**

In this study, the mood will be assessed using the DASS scale, and social interaction will be measured using the Berkman-Syme SNI. The baseline measures for the 2 groups will be compared using analysis of variance. In addition, changes in these measures over time will be compared for the 2 groups of respondents using an ITT RMMM, controlling for age, gender, and education level and any variable that differs markedly between the groups at the baseline.

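### Entered as main effects, age, gender and education cancel from the two-visit group-by-time estimate, so the comparison of 6-month change is effectively unadjusted for covariate-related differences in change

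*Protocol article*

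**What the plan says.** Under Primary Statistical Analyses, a "repeated measures mixed model group (no hearing aid vs hearing aid users) x Time (Time 1 vs Time 2) analysis (RMMM) will be used for" every analysis in the study. The same section adds "In the ITT RMMM analyses, the autoregressive (AR) dependence will be assumed" and "The missing data will be accommodated in this analysis", with an exception for whole-brain fMRI, which uses completers only.

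Under Cognitive Data, changes in SUCCAB "values over time will be compared for the 2 groups of respondents using an ITT RMMM, controlling for age, gender, and education level"; a baseline variable that is clearly imbalanced is to be added. Under Mood and Social Interaction Data, the rule for changes in DASS and SNI is the same: "measures over time will be compared for the 2 groups of respondents using an ITT RMMM, controlling for age, gender, and education level", again with any clearly imbalanced variable added.

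On allocation and matching by hearing loss, Study Design states that "group randomization is not possible in this study; however, the groups will be matched as much as possible in terms of the degree of hearing". No other matching variable is named. Study Hypotheses sets new users against long-term users after 6 months, so the group-by-time term carries the main hypothesis.

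**The concern.** In a non-randomised comparison, the listed covariates are the only stated protection against group differences other than degree of hearing loss. A reader of the results would take the group-by-time estimate to be adjusted for age, gender and education.

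In a two-visit model, however, a main effect of something that does not vary within a person cannot alter a within-person contrast. If new users differ in age or education from long-term users, and practice gain or decline over 6 months depends on those variables, the resulting difference in change would be read as an effect of hearing aids, under an adjusted label.

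**Working it through.** **The plan's own figure.** Study Power Analysis allows 10% attrition (30 × 0.9 = 27 per group) and gives a detectable interaction of d = 0.77 at 5% and 80% power. Two-sided, by the normal approximation, (1.960 + 0.842) × √(2/27) = 0.763; by the t distribution it is 0.777. Power at d = 0.77 is 0.808 and 0.793 respectively. The figure reproduces, and it contains almost no gain from covariates (implied R² about 0.02).

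**Algebra.** For person i at visit j, with group G, time T (0 or 1) and person-constant covariates X:

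Y_ij = β0 + β1·G_i + β2·T_j + β3·G_i·T_j + γ′X_i + e_ij

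The change is D_i = Y_i2 − Y_i1 = β2 + β3·G_i + (e_i2 − e_i1). The term γ′X_i has gone. With complete data the estimate of β3 is the raw difference in mean change, whatever X contains. With two visits an AR(1) structure is a single correlation, the same as compound symmetry, so it does not alter this.

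If change really depends on X through a term δ′X_i·T_j that is left out, the bias in β3 is δ′ × (group difference in mean X). Only covariate-by-time terms remove it.

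**Check by simulation.** None of these inputs comes from the article: 30 per group, true interaction 0, groups 1 SD apart in age, outcome change of 0.3 per SD of age, 150 data sets, AR(1) model fitted by REML. The bias expected from the algebra is 0.3 × 1 = 0.30.

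| Data | Model | Mean interaction | Mean SE | Rejected at 5% |
|---|---|---|---|---|
| Complete | No covariates | 0.293 | 0.198 | 33% |
| Complete | Covariate main effects | 0.293 | 0.198 | 33% |
| Complete | Covariate × time | −0.009 | 0.210 | 5% |
| 10% dropout | No covariates | 0.310 | 0.206 | 36% |
| 10% dropout | Covariate main effects | 0.311 | 0.205 | 36% |
| 10% dropout | Covariate × time | 0.026 | 0.224 | 6% |

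With complete data the first two models differed by at most 3 × 10⁻¹⁵ in the estimate and about 10⁻⁸ in the SE. An unstructured covariance, tried on one data set, gave the same estimate. With 10% dropout they differed by 0.014 on average (0.014/0.205 ≈ 0.07 SE) and 0.072 at most, and the bias stayed. The residual 0.026 in the last row is within simulation error (0.224/√150 = 0.018).

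**How the bias scales.** The inputs are again assumptions: 27 per group, test–retest correlation 0.7, 8,000 simulated change-score data sets per setting.

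| Age gap (years) | Slope of 6-month change (SD per year of age) | Bias = gap × slope (SD) | False-positive rate |
|---|---|---|---|
| 5 | 0.02 | 0.10 | 7% |
| 5 | 0.03 | 0.15 | 10% |
| 5 | 0.05 | 0.25 | 19% |
| 8 | 0.03 | 0.24 | 20% |
| 8 | 0.05 | 0.40 | 39% |

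With a gap or slope of zero the bias is zero. Over the eligible range of 55–90 years, a slope of 0.02 implies 35 × 0.02 = 0.70 SD difference in 6-month change between its ends, and 0.05 implies 1.75 SD. The upper rows are therefore strong assumptions.

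**The case against.** The strongest reply is that the article gives no model equation. It says the comparison of changes is what is controlled, and taken literally that would require covariate-by-time terms; a full analysis plan may contain them. This stands in part: the wording does not rule such terms out, so it cannot be said that the plan excludes them. But the article does name the model and its one interaction, and lists the covariates beside it. An analyst following it as written would fit main effects and report an adjusted test that is numerically the unadjusted one. That goes beyond omitted detail.

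Three stronger readings are tempting, and the document does not support them.

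- A reader might infer that age, gender and education confound the result in every respect. They do not: the within-person contrast already removes whatever is constant over time. The baseline ANCOVA for SUCCAB is adjusted as stated and is unaffected.
- A reader might take 39%, or the simulated 33%, as this study's error rate. Nothing in the article gives an age gap, its direction, a test–retest correlation or an age slope of change.
- A reader might extend the fault to imaging. The speech-task and structural T1 sections name no covariates, so they claim no control that fails.

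**Conclusion.** The point holds on the plain reading of the three analysis sections. The covariates listed there, including any added for baseline imbalance, do not act on the group-by-time estimate: exactly so with complete data, and to within about 0.01 on average with 10% dropout in simulated data. The cancellation needs no assumption beyond main-effect entry and values fixed within a person.

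What is left unadjusted is confounding of the 6-month change. Its size here cannot be known from the document, so the false-positive figures are illustrative only.

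**What to change.** State that the ITT mixed models for SUCCAB, DASS and SNI include age × time, gender × time and education × time together with group × time, and the same term for any baseline variable added because of imbalance. If such terms are already intended, one sentence saying so settles the point.

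Keep the mixed model. A regression of the 6-month change on group and covariates matches it only with complete data, and would drop participants without follow-up whom the ITT analysis is meant to retain. Extending the terms to the imaging models is optional.

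Cost: one sentence, and about 3 degrees of freedom if education enters as a single term, which alone moves the detectable d from 0.777 to 0.778. If covariates correlate with group there is also variance inflation. For age alone, with equal groups, the factor is 1 + (gap/SD)²/4. Assuming an age SD of 7–8 years:

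- gap 5, SD 8: 1 + 0.625²/4 = 1.10; detectable d = 0.778 × √1.098 = 0.815
- gap 8, SD 7: 1 + 1.143²/4 = 1.33; detectable d = 0.778 × √1.327 = 0.896

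That is about 0.81–0.90 before any precision gained from covariates that predict change. In the simulation, where age did predict change, the mean SE rose from 0.198 to 0.210 with complete data. Differences between the self-selected groups that are not measured remain after the fix.
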